### Research questions

The following research questions are posed:Will music therapy (TMI) be as effective as standard treatment regarding the decrease of TSD symptoms (primary outcome) from pre to post treatment and from pre-treatment to 6 months’ follow-up?Will music therapy (TMI) be as effective as standard treatment regarding the decrease of dissociation and the improvement of attachment style and well-being (secondary outcomes) pre to post treatment and from pre-treatment to 6 months’ follow-up?Does any variable from the patient data at baseline (i.e., gender, age) specifically correlate with good outcomes of music therapy on trauma symptoms compared to standard treatment?Concerning patient satisfaction with therapy sessions, is there a difference between music therapy and verbal therapy, and is there any development in the assessment of the sessions during the therapy course?Will basic levels of salivary oxytocin, beta-endorphin and substance P be changed by the treatment, are any changes stable at follow-up, and are there differences between the two groups?Will the levels of salivary oxytocin, beta-endorphin and substance P be affected by one session, and are there a difference between the groups, and between a session at the beginning and in the end of treatment?

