## Interventions

The refugee clinic carries out trauma treatment in a multidisciplinary clinical setting. The current study compares only the psychotherapeutic part of treatment, but for ethical reasons all other services (social counseling, body therapy, health advice) in the clinic are kept open for all participants as needed, and the extent of other services will be monitored throughout the study. All participants who receive medication as part of the treatment in the experimental group as well as the standard treatment group are monitored continuously by the physicians during the whole course of psychotherapy. Differences between groups are analyzed as possible confounders related to outcome.

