#### Procedures

After assessment by the visitation team and at the team conference, eligible patients are invited to participate in the study by one of the three music therapists/researchersThe patient is informed orally and in writing about the studyIf the patient accepts participation, informed consent is signed by patient and therapist. If participation is rejected the patient is offered other treatment in the clinicBaseline measurement is carried out by the music therapists/researchers. Information about health according to height, weight, exercise, use of alcohol, smoking habits, symptoms and medication is collected during the visitation procedures in the clinic, and transferred to the dataset by the researchers. All data collection is carried out on laptops with a data collection environment called Xpsy (see below in the “Data management” section). Demographic data and information relevant for the trauma history are collected and scored regarding age, gender, country of origin, native language, education, civil state, number of children at home, whether the patient has been sexually or physically abused during their childhood, imprisonment (number of weeks), exposure to torture, number of weeks on flight, number of weeks in refugee camps and/or asylum centers. The patient fills out self-report questionnaires and a saliva sample is collected. The scoring of the primary questionnaire HTQ is done by a psychologist or trained music therapist, as it requires specialist knowledge and training, and is based on an interview with the patient. The secondary questionnaires are filled out in the presence of one of the researchers or with the presence of a translator trained in assisting the scoring of the questionnairesThe patient is randomized to treatment with music therapy or standard treatmentTreatment is carried out according to the descriptions under “Interventions”Patient data are recorded in all sessions (session evaluation), session data regarding use of music and themes for the therapy are collected by the music therapists with the help of translatorsData collection (PTSD-8) is carried out in sessions 6 and 11 and saliva samples are collected in sessions 3 and 14 (see “Outcome measures” and the flow chart in Fig. 1)After the last session, a post-treatment data collection session is scheduled, where all questionnaires are filled out, HTQ is scored by an external psychologist (and translator) who is not a part of the treatment team and who is blinded to the patient’s treatment group. Three questions regarding the patient’s own evaluation of their current life situation are posed by the music therapist/researcher. In order to leave out confounders of diurnal variation, the time of the meeting is scheduled so that the collection of saliva can occur at the same hour as the baseline sample was collected. Any need for additional treatment is assessed by the clinical team. If additional psychotherapeutic treatment is needed, the participant is excluded from follow-up measurement. All participants who have completed the protocol are invited to a 6-month follow-up session, where questionnaires and saliva samples are collected, with an external psychologist assisting in scoring HTQ, and a trained translator, who is blinded to the affiliation, assisting in scoring the remaining questionnaires

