#### Statistical methods

Statistical analysis will be carried out in the statistical environment R [82] in cooperation with the statistical department in the research unit of Region Zealand and PFI Region Zealand (Production, Research and Innovation Unit). Data will be treated according to the intention-to-treat principle. Analysis of all data will take place after the conclusion of data collection. Following the initial screening of the data significance tests concerning differences between standard treatment and music therapy will be carried out in order to assess the non-inferiority of music therapy. Significance and variance for the primary outcome measure will be calculated with analysis of covariance (ANCOVA), including data from five measuring points. Secondary questionnaire outcome data will also be calculated with ANCOVA, using three data points. Correlations between trauma symptoms, attachment, dissociation and demographic parameters are investigated. A regression analysis will be applied to look for predictors of improvement of trauma symptoms (HTQ) and change of attachment style, as well as predictors for improvement connected to treatment (music therapy or standard treatment). Analysis of hormones will be split up in an ANCOVA testing variance between groups and with time (baseline to follow-up), and simple significance tests of change after single sessions (between the third and 14th session and between the interventions). Session satisfaction data will be treated with descriptive statistical methods.

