#### Potential harms

Potential harms of the trial can occur as harms of the interventions as well as harms of the research procedures. Music therapy is a relatively new treatment modality for refugees, and the art of choosing music for the right phase of treatment is still being developed. According to the pilot study, the treatment method is not harmful when used with care and ongoing attunement to the needs of the patient, but the music therapists must pay attention to avoid adverse reactions in case of hypersensitivity to sound, restimulation of trauma by using too loud or dynamic pieces of music, or restimulation of trauma in former musicians or persons who have been tortured with sound or music. Music listening that triggers trauma memory has been found to happen frequently and, therefore, the music therapists have to be specifically trained when working with this clinical group. Trauma exposure with music is very effective, but it requires that both the patient and the therapist can work together to keep arousal at a manageable level. The patient is given control over music choice and volume, and is educated to give feedback before, during and after music listening, as well as how to use music safely at home.

It is well-known, that the exposure phase of trauma treatment both in music therapy and standard treatment will stir up traumatic memories which can worsen the symptoms for a period. The patients are informed about this and supported to cope with the symptoms. The therapists can go back to stabilization work whenever needed to facilitate a safe therapeutic course of treatment. Some of the patients express a need for longer treatment periods, that collides with the six months’ follow-up period without treatment. The therapists normally have the same amount of time for each patient as planned for in the study, and the closure of therapy is planned for with care. However, some patients happen to be re-traumatized by external events, and in such cases the treatment team of the clinic can estimate whether they can receive additional treatment and be excluded from follow-up measures in the study.

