### Risk of bias

In a psychotherapy trial such as this, it is often not possible to blind the intervention of the participants, and there can be an influence of their knowledge of being in the intervention or the control group. However, in this trial we investigate two types of treatment in a single clinic with equal dose (16 sessions) and equal weight as primary trauma treatment modalities. According to concealment of allocation, the randomization procedure is generated by computer software at Sealed Envelope, and none of the researchers have any influence over the procedure. Baseline tests are carried out before randomization, so that the allocation does not influence the measurement. Psychologists carrying out data collection concerning the primary outcome measure at post and follow-up times are concealed to the allocation (and the patients are not asked about it). Imbalances between treatment groups are prevented by the use of stratification (gender and location).

As music therapists carry out the information meetings and measurement, the participants might be more motivated for music therapy than standard treatment (comparator), and be more likely to drop out from standard treatment. This could possibly influence the results in favor of music therapy. Adherence to the treatment is secured, as none of the participants can cross over to the other group. If a patient drops out from music therapy and is offered standard treatment, they are excluded from follow-up. If participants are offered other types of treatment in the clinic parallel to the assigned treatment, this will be monitored and an analysis of any group differences will be carried out.

Protocol fidelity is assured by data collection of the therapist notes for all sessions, by team supervision and frequent meetings between music therapists and psychologists and in the group of music therapy researchers. The use of Xpsy for data collection ensures that no participant data are analyzed in the wrong group.

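### Planned exclusion from the 6-month assessment contradicts intention-to-treat and leaves a selected comparison, with bias of unknown size and direction, for part of the primary question

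*Protocol article*

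**What the plan says.** On analysis, Statistical methods states: "Data will be treated according to the intention-to-treat principle". The primary ANCOVA is described as "including data from five measuring points". Counting from the Trial design section, these are baseline, two short-form assessments during therapy, the end of therapy and the 6-month follow-up. Research questions gives the time frame for the first question as "primary outcome) from pre to post treatment and from pre-treatment to 6 months’ follow-up".

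On measurement, four statements limit who is seen at 6 months:

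- Procedures: "If additional psychotherapeutic treatment is needed, the participant is excluded from follow-up measurement".
- Procedures: "All participants who have completed the protocol are invited to a 6-month follow-up session".
- Potential harms, for patients traumatised anew by outside events: the treatment team may judge "whether they can receive additional treatment and be excluded from follow-up measures in the study".
- Risk of bias: "If a patient drops out from music therapy and is offered standard treatment, they are excluded from follow-up". The sentence just before it says that switching to the other arm is impossible.

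Power calculation sets a minimum of 64 participants (32 per group) from a margin of 0.3 and an SD of 0.48 on post-treatment HTQ. It raises this to 70 for 10% dropout.

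**The concern.** Intention-to-treat needs outcomes sought from everyone randomised, whatever therapy they went on to receive. Under the quoted rules, a clinical judgement made after randomisation decides whether the 6-month HTQ is collected at all. The team that makes it is not blinded to arm; the Blinding section conceals allocation only from the external HTQ raters.

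A patient judged to need more psychotherapy, or who has left the assigned therapy, will on average probably differ in HTQ from one who has not. The 6-month values are then missing for reasons related to outcome or treatment course, and the groups compared are no longer the randomised groups. In a non-inferiority trial this matters because a real deficit in either arm could be partly hidden. The protocol foresees such cases: Potential harms says that some patients want longer treatment and that this conflicts with a treatment-free follow-up. It gives no rate.

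**Working it through.** **1. Do the statements conflict?** Set side by side, Statistical methods commits to intention-to-treat and to a primary analysis that uses the 6-month point. Procedures, Potential harms and Risk of bias commit to not measuring defined groups at that point. No section provides for measuring them or says how they enter the analysis. The conflict is in the stated rules, so it is not a detail left to an analysis plan.

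**2. The plan's own sample size.** Inputs from Power calculation: margin 0.3, SD 0.48, significance level 0.05 (sidedness not stated), and power printed as 0.08, read here as 0.80. With a true difference of 0:

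n per group = 2 × (z₁₋α + z₁₋β)² × SD² / margin²

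At one-sided 0.05: 2 × (1.645 + 0.842)² × 0.48² / 0.3² ≈ 31.7, so 32 per group and 64 in total. This matches the plan. At one-sided 0.025 the result is 41 per group, which does not match.

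**3. Power at 6 months.** Power = Φ(0.3 / (0.48 × √(2/n)) − 1.645), starting from 35 per arm. The post-treatment SD is assumed to hold at 6 months, and the loss rates are assumed.

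| Total loss per arm | n per arm | Power |
|---|---|---|
| 10% | 31.5 | 79.8% |
| 20% | 28 | 75.6% |
| 30% | 24.5 | 70.6% |

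The 10% allowance is used up by ordinary dropout, and nothing is left for planned exclusions.

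**4. Bias in the contrast.** Let fT and fC be the shares excluded in the music and standard arms, and D the amount by which excluded patients score worse on HTQ than those measured. Each arm's all-randomised mean equals its measured mean plus f × D. With a common D:

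all-randomised difference − measured difference = (fT − fC) × D

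The protocol gives neither f nor D, so every row below is an assumption.

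| fT | fC | D | Shift | Share of 0.3 margin |
|---|---|---|---|---|
| 15% | 15% | any | 0 | 0% |
| 20% | 10% | 0.3 | 0.03 | 10% |
| 20% | 10% | 0.5 | 0.05 | 17% |
| 30% | 10% | 0.5 | 0.10 | 33% |
| 30% | 10% | 1.0 | 0.20 | 67% |
| 10% | 20% | 0.5 | −0.05 | 17%, against music therapy |

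A positive shift means that the measured comparison flatters music therapy. With equal rates and equal gaps the contrast is unbiased, but both arms' 6-month means look better than they are.

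**The case against.** Several stronger readings are tempting, and the documents do not support them.

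- *A reader might infer that the bias favours music therapy.* The rules in Procedures and Potential harms apply to both arms, and non-completers of either therapy go uninvited. The dropout rule in Risk of bias names only music therapy, but the completers-only invitation makes that largely a difference of wording. The same section expects more dropout from standard treatment. It supposes that this would favour music therapy, but if the patients lost are the poor responders, the measured standard arm improves and the shift goes the other way.
- *A reader might infer that treatment failures are being removed.* Some exclusions follow outside events, which are not failures of therapy.
- *A reader might infer that the loss is beyond any repair in analysis.* The blinded post-treatment HTQ comes before the need-for-more-therapy exclusion, and short-form scores are taken during therapy. A repeated-measures model could use these to reduce the bias, though it cannot be relied on to remove it. Less is available for early dropouts.
- *A reader might infer that the primary contrast will be adjusted for other services and medication*, since Interventions says "Differences between groups are analyzed as possible confounders related to outcome". Neither that section nor Statistical methods says so, and nothing here rests on it.

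It can also be argued that the authors wanted to know whether gains last without further therapy, since Potential harms describes a treatment-free follow-up. That is a legitimate question, but it is not intention-to-treat, and Statistical methods does not state it.

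These points limit the direction, size and reach of the problem. They leave the contradiction in place.

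**Conclusion.** The point stands in limited form. The protocol plans not to measure some randomised participants at 6 months, for reasons that arise after randomisation and are likely related to outcome or treatment course. This contradicts its intention-to-treat statement and affects one of the two time points in the first research question, as well as the last of the five points in the primary ANCOVA. The need-for-more-therapy rule leaves the post-treatment HTQ, on which the sample size rests, untouched.

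The size and direction of the bias cannot be determined from the document. A 10 to 20 percentage point imbalance in exclusions with a 0.5-point gap would shift the contrast by 17% to 33% of the margin, in whichever direction the imbalance runs. The loss of power is modest: about 76% at an assumed 20% total loss, on a one-sided 5% level inferred from reproducing the plan's 64.

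**What to change.** Delete the rules that exclude participants from follow-up measurement in Procedures, Potential harms and Risk of bias, and replace the completers-only invitation. Invite every randomised participant who has not withdrawn consent to the post-treatment and 6-month HTQ, whatever therapy was completed or added, and analyse each in the randomised arm. Record further or different psychotherapy with its date and examine its influence in a sensitivity analysis. Reconcile the Risk of bias statement that switching arms is impossible with the adjoining rule on music therapy dropouts offered standard treatment. Who receives further treatment is left as it is.

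The cost is a protocol amendment, which the Protocol amendment section routes through the regional committee, and a few more follow-up visits within the planned 70. The blinded external psychologist already carries out such visits. The downside is one of interpretation: the 6-month contrast then reflects the assigned therapy plus any later treatment. The change should be made early, because a 6-month score not taken on time cannot be recovered.

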### Data management

All data related to the study are stored with highest possible level of security. Questionnaire data, session evaluation and demographic data (including health and trauma history data) are typed into a database with the program Xpsy, which is a quality assurance system for psychiatric clinics developed by PsyMeta Gmbh by [name], Shafisheim in Switzerland (https://www.xpsy.eu/). It is administered by the co-researcher and data manager (second author SM). All the questionnaires are set up in electronic versions in the program in three languages, and are stored in the database as soon as they are typed in. The program ensures that all data can be typed by the participants and/or translators without missing any questions, the data time point for the single participant is clearly indicated and the dates of entering the system can be monitored. All patients have their own login based on ID number. Researchers have a common code to access the participant’s actual session or questionnaire session, and typing in of demographic data.

### Data confidentiality

The project is approved by the Danish data management authorities “Datatilsynet” under the protocol number REV-50-2014. Data are stored until the completion of analysis and are then deleted. Saliva samples are stored until 2027 in case of the need to go back and do additional analyses. In that case all participants will be asked for additional consent.

The research data typed into the Xpsy database are stored on a secured server that is placed in a locked cabinet. Confidential data regarding patients, such as list of patients in the study, reasons for decline of participation for eligible patients and list of completed saliva samples are stored at a protected website for clinicians at the Clinic of Traumatized Refugees. Any other data, such as informed consent contracts, clinical notes, patients’ drawings, are stored in locked cabinets. Patient data related to treatment, other than research data, are stored in the patient database OPUS, Region Zealand, or after 25. November 2017 in the application “Sundhedsplatformen.”

Saliva samples are stored in research freezers placed in locked local facilities.

For the data analysis, the members of the Steering Group and the group of three music therapist/researchers will have access to data, stored under ID numbers in the Xpsy environment. Access will also be granted to the statistical consultant who works in the same organization (Region Zealand). A signed data agreement contract is made between the Regional Zealand and Aarhus University for exchanging information on the saliva data.

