### Trauma-focused Music and Imagery (TMI)

TMI is an adaptation of GIM, a music therapy method initiated by the American music therapist Helen Bonny in the 1970s [53, 69] using music listening of selections of classical music in an altered state of consciousness as a medium for therapeutic change. During the listening experience, a non-directive verbal dialog between patient and therapist is carried out supporting the deepening and integration of the ongoing stream of imagery, emotions and sensations evoked by the music. GIM has served as primary psychotherapeutic treatment in a range of clinical settings and has been modified and adapted to several clinical populations [70]. A continuum of practices exists, from the full Bonny method (2-h sessions with challenging music and verbal dialogue) to short GIM (1-h sessions, shorter music selection); music and imagery being a supportive short-form that often only includes one or a few short music pieces and no verbal interaction during the music listening part.

A GIM therapist holds a master’s degree in music therapy or other relevant subject followed by a minimum of 3 years of supervised training in the GIM method licensed by an international training institute (see www.music-and-imagery.eu).. The method has been adapted to refugee trauma treatment by the authors [name], [name] and [name] [62].

A TMI session includes:A verbal conversation used to check in and talk about actual issuesAgreement of a focus for the music listeningFinding a music piece (patient chosen or therapist chosen; if the therapist chooses the piece a small excerpt is played to assess the match of music with the patient). Music from several genres are optional: classical, film, meditative music, or music corresponding to the patient’s cultural backgroundMusic listening; the patient is sitting on a chair or lying on a couch, eyes open or closed as preferredA short induction; for example, mindful focus on breathing, guided relaxation or focus on an inner imageMusic listening (2–10 min in the beginning, up to 20 min in the end of therapy). The therapist can talk during the music if helpfulThe therapist guides the patient back to the presentParticipants are invited to draw a picture of the imageryVerbal communication about the drawing and the experience with the focus on integration of important imagery, acknowledgement and meaningfulness in the therapeutic processHomework assignment as needed (including using music at home)

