#### Randomization

Randomization is carried out with the help of the randomization software Sealed Envelope (https://sealedenvelope.com/). Stratification is applied regarding geography (three different locations) and gender (male/female). Within the strata, random permuted blocks of even length (blocks of four or six participants) are used. When a participant has given informed consent and completed baseline measures with one of the three music therapists who takes care of the research procedures (one in each location), the music therapist/researcher logs on to the randomization website and types patient ID number, gender and location. Information of the treatment group is provided immediately on the website and is also sent by email to the researcher. The status of the patient is typed into the Xpsy database, and the patient is referred to either music therapy or standard treatment at the location.

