#### Blinding

There is no blinding connected to the randomization of intervention. Questionnaire data are blinded to all clinicians who are performing the treatment and data collection in the project, so that none of the clinicians or researchers have access to completed questionnaire data from their own patients or any other participant in the trial. This ensures that the clinical processes are not influenced by the outcome results data.

External psychologists are called in to assist the scoring of HTQ post treatment and follow-up, they are blinded to the treatment of the participant. Data remain concealed until the entire trial is completed.

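### The music therapist/researchers who learn each patient's arm at randomisation are given ID-keyed data for the analysis, and no masking is stated for the data screening or the primary non-inferiority test

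*Protocol article*

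**What the plan says.** All references are to the protocol article.

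- **Data confidentiality.** Access at the analysis stage is set out as follows: "the members of the Steering Group and the group of three music therapist/researchers will have access to data, stored under ID numbers". The database concerned is Xpsy. A statistical consultant employed by the same region also gets access.
- **Randomization.** Three music therapists, one per location, handle the research procedures. After baseline, "the music therapist/researcher logs on to the randomization website and types patient ID number, gender and location". The arm is then disclosed to that person: "Information of the treatment group is provided immediately on the website and is also sent by email to the researcher". A further entry is made at this stage: "The status of the patient is typed into the Xpsy database".
- **Blinding.** "There is no blinding connected to the randomization of intervention". The external psychologists who assist HTQ scoring after treatment and at follow-up are blinded, and questionnaire data are withheld from clinicians and researchers until the trial is complete.
- **Auditing.** Researchers have no data access until data collection has ended.
- **Statistical methods.** Data are handled by intention to treat, in cooperation with the regional statistical department. The sequence is given thus: "Following the initial screening of the data significance tests concerning differences between standard treatment and music therapy will be carried out". The purpose stated for these tests is to judge non-inferiority. The primary outcome is analysed by ANCOVA using five measuring points.

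**The concern.** The protocol treats knowledge of allocation as a source of bias. It brings in blinded HTQ raters, and under Risk of bias it warns that the music therapists' role in information meetings and measurement could favour music therapy. The stated protection ends when the analysis begins. At that point people who know the arm behind each ID receive the outcomes under the same IDs, and a screening step of unspecified content comes before the primary test.

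Screening and model set-up usually involve judgement: how to treat an implausible value or a visit far out of window, and how to combine the mid-treatment PTSD-8 scores with the HTQ in one ANCOVA. Such calls are safest when made without sight of the arm. With about 35 patients per arm and a margin of 0.3 HTQ points, a few of them can matter.

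**Working it through.** **1. Are ID-keyed data masked for these researchers?**

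- Randomization: the researcher enters the patient ID and receives the arm on screen and by email. Each of the three can therefore link ID to arm for their own location, and together they cover all three.
- Data confidentiality: the same three receive data keyed by ID for the analysis.
- Taken together, the ID coding protects confidentiality but does not mask the arm. Patient status is also entered in Xpsy. The article does not say that status includes the arm, but the argument does not need it to.

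**2. Does any other stated safeguard cover the analysis?**

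- The blinded raters protect the scoring of HTQ.
- The concealment under Blinding and Auditing protects trial conduct, and it ends with the trial or with data collection.
- Statistical methods mentions neither coded arms nor a masked review, and does not describe the consultant as masked.

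**3. The plan's own sample size, to fix the error level for an illustration.**

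Inputs from Power calculation: margin 0.3, SD 0.48, significance level 0.05 (sidedness not given), power printed as 0.08 and read here as 0.80.

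n per arm = 2 × 0.48² × (1.645 + 0.842)² / 0.3² = 31.7, so 32 per arm and 64 in total. This matches the stated 64, so the plan's figure corresponds to a one-sided 5% test with no true difference. A one-sided 2.5% test would need 41 per arm, or 82.

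**4. What an arm-aware exclusion would do, if one occurred.**

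Assumptions: 35 per arm; true difference exactly at the 0.3 margin; one-sided 5%; k music-arm patients dropped, each 2 SD (0.96 points) above the arm mean, a higher HTQ score being worse.

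- Shift in the music-arm mean = k × 0.96 / (35 − k)
- SE = 0.48 × √(1/35 + 1/(35 − k))
- False non-inferiority rate = Φ(−1.645 + shift/SE)

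| k | Shift | SE | Shift/SE | False non-inferiority |
|---|---|---|---|---|
| 0 | 0 | 0.115 | 0 | 5.0% |
| 1 | 0.028 | 0.116 | 0.244 | 8.1% |
| 2 | 0.058 | 0.116 | 0.500 | 12.6% |

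A simulation (200,000 trials, pooled t interval) that drops the worst one or two music-arm scores gives 8.7% and 13.1%, against 5.0% with none dropped. With 32 evaluable patients per arm the formula gives 8.2% and 13.1%.

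**The case against.** **Masking may be in a document not shown.** Arm-coded exports, screening rules and a blind data review are often left to the SAP, and the access statement sets no order. Investigators could be given access after a masked primary analysis. This stands in part: the absence of screening rules is not the point. The access rule, however, is stated in the article. A masking step added elsewhere would leave these three unmasked unless their access came later or the IDs were changed.

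**A reader might infer that the three researchers run the screening and the non-inferiority test themselves.** The documents do not support this. They say who has access, and that the analysis is done in cooperation with the statistical department. They do not say who screens or tests.

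**A reader might also infer that screening will remove outliers or awkward patients.** The article does not define the step. It states intention to treat, which argues against dropping patients with observed poor scores. The illustration in the working would need a departure from that principle. Judgement on doubtful values, or on how the five-point model is built, would not.

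**A reader might take these three to be the developers of the therapy.** The article says "The method has been adapted to refugee trauma treatment by the authors", but names are removed here and the statement cannot be tied to them. Implications expresses only a general hope that the results will support wider use of music therapists.

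**Other controls are real.** HTQ raters are blinded, Xpsy prevents skipped questions and lets entry dates be monitored, and the 0.3 margin and ANCOVA are stated in advance. These narrow the room for judgement but do not remove it.

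**Conclusion.** The point holds as a weakness in the stated access arrangement. People who know the arms by ID are given ID-keyed data for the analysis, and nothing in the article masks the screening or the primary test. It is not evidence that biased decisions will be made.

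Any effect on the error rate is hypothetical. The rise from 5% to about 8% for one dropped patient, or about 13% for two, assumes a true difference at the margin, a one-sided 5% test, and exclusions that all fall on poor scorers in the music arm. With no such exclusion there is no change. This is a cheap improvement of minor to moderate priority.

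**What to change.** Amend Data confidentiality and Statistical methods to set this order:

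1. The statistical consultant first receives an export, in place of Xpsy access, with new study IDs and arms coded A/B. New IDs are needed because the existing ones reveal the arm to the researchers.
2. The file holds the strata (location and gender) and every score the five-point ANCOVA needs: baseline, post-treatment and follow-up HTQ, and the two mid-treatment PTSD-8 scores. Session-level music items stay out because they reveal the arm.
3. Someone in the statistical department who is not doing the analysis holds the allocation key. It is sensible for that person to do the recoding too, since a co-researcher administers Xpsy.
4. Before the code is broken, the consultant records the screening decisions and the A-minus-B estimate with its confidence interval. Non-inferiority can then be read either way: upper limit below 0.3 if A is music therapy, lower limit above −0.3 if B is.
5. Only then do the Steering Group and the music therapist/researchers get access.

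The cost is a few sentences in the plan, one extra export step in a department already engaged, and a short delay before the researchers see the data. Trial conduct is unaffected.
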